### Drop-outs

All parents and children who consent to take part in the study will be followed from the moment of randomization till the follow-up assessment nine months later. To prevent drop-out parents and children are actively motivated by therapists and researchers to remain in the program and the study. Practical limitations are, as far as possible, removed, for example by arranging child care and transportation. If parents and children drop out of the program and are not able to come to the post-test and/or follow-up assessment, questionnaires will be mailed to the last known address and they are reminded by phone and email to complete the questionnaires. If children are not literate enough to fill out the questionnaires by themselves, only the parent is asked to fill out the questionnaire. The teacher is also sent a questionnaire by mail. If, after several reminders, the questionnaires are not sent back, the principle of last value carried forward will be applied. The reasons for drop-out will be documented and analyzed and the results will be reported back to the organizations participating in the study, so they may use this information to combat drop-out.

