### Study population

140 children (6-12 years of age) and their caregiving custodial parents who experienced interparental violence will participate in this study.

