**Figure 1 F1:**
[figure not shown]
**Research procedure**. After informed consent is obtained, 2/3 of all parent-child dyads will be randomized into the experimental arm and 1/3 into the control arm. Parents and children are asked to fill out questionnaires (parent: TSCYC, CBCL, Questionnaire about duration and severity of domestic violence, demographic questionnaire, IES-R, HADS, PSI; child: CDI, TSCC, Questionnaire for children how to cope with difficult situations) at the first assessment (T1). A week later the program starts for all parents and children. One week (T2) and six months (T3) after the end of the program parents and children who take part in the study are again invited to fill out questionnaires and participate in two observation tasks (FIT and AEED). To check up on parents in the period between T2 and T3, parents are contacted by phone two times. At all assessments the teacher is also sent a questionnaire.

Parents receive €15,- after completing the first assessment, €25,- after participating in the program and completing the second assessment and €40,- after completing the follow up assessment. Children receive a gift after each assessment.

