### Sample size calculation

The total sample size is based on the expected differences in outcome measures between children participating in the secondary prevention program 'En nu ik...!' and the control program 'Jij hoort erbij'. Because the effect of the intervention program has been tested before in a non-experimental design [22], a conservative estimate of f = 0,25 [59] is made about the effect size. Based on an alpha of .05, a power of .80 in a two tailed test, 48 subjects in each condition are needed.

To answer the research questions concerning the influence of potential mediators and moderators on the effectiveness of the secondary prevention program, several multiple regression analyses with different predictors will be performed. Based on an alpha of .05, an expected medium effect size of f^2 ^= 0.15 and a N = 90 we will be able to achieve a power of .80 for a model with up to five predictors. In smaller models of up to two predictors it will also be possible to draw conclusions about the independent contribution of each predictor.

Because of the tumultuous time these families are in we expect a relatively high drop-out rate of around 45% from T1 to T3. For this reason, we aim to recruit 250 children and parents.

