### Data analyses

Most analyses will be done using the software program SPSS. Intention-to-treat and completer analyses will be performed. Descriptive analyses will be carried out by standard methods. The change in behavior will be assessed on a continuous scale, taking into consideration the scale of the different variables. For analyses of the primary outcome measures, we plan to use ANOVA repeated measure analyses and the scores of the children in the intervention group will be compared with their own scores on a previous assessment, as well as with scores of children in the control group at the same assessment. Mediator and moderator models will be tested, using data of all children (intervention and control group). Analyses and reporting of the results will be done according to the CONSORT 2010 Statement-guidelines [60].

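### Last value carried forward is the only stated rule for unreturned questionnaires at 45% expected drop-out; it can distort the T3 arm difference and makes it look too precise

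*Protocol article*

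**What the plan says.** Under Drop-outs, families who leave the program are mailed the questionnaires and reminded by phone and email. If the questionnaires still do not come back, "the principle of last value carried forward will be applied". The same section puts the follow-up assessment nine months after randomization.

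Under Sample size calculation: "we expect a relatively high drop-out rate of around 45% from T1 to T3", and "For this reason, we aim to recruit 250 children and parents".

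Under Data analyses: "Intention-to-treat and completer analyses will be performed". The primary outcomes are to be analysed by repeated-measures ANOVA. No other treatment of missing scores is named. The article does not say in so many words that carried-forward scores enter the intention-to-treat set, but taking Drop-outs and Data analyses together that is the only natural reading.

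**The concern.** Carrying a score forward asserts that the child did not change after the last completed assessment. For a child lost before T2, that means no change for up to nine months. The Background does not support this. It describes distress after a frightening experience as usually passing, and it also says that problems may develop after the parental conflict has ended. Scores may move either way.

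Three things follow. If loss is equal in the arms and some of it comes before the effect has appeared, a real difference is diluted. If loss differs between arms while children in both arms change, part of that common change appears as a treatment difference, with a sign set by which arm lost more. In either case the filled-in scores count as full observations, so the T3 comparison looks more precise than the data allow.

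**Working it through.** **Reproducing the plan's figures.** Allowing for 45% loss from 140 gives 140 / (1 − 0.45) = 255, against the stated 250. Conversely 250 × 0.55 = 137.5, close to the stated 140. The 45% is therefore a working planning figure. Of 250 children, 0.45 × 250 ≈ 112 T3 values would be carried forward.

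**Inputs from the document.** Recruitment 250; drop-out 45%; two thirds to the intervention arm (Figure 1 legend), hence 167 v 83; effect f = 0.25, which is d = 0.50 for two groups.

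**Inputs assumed.** SD 1 at each assessment; correlation 0.6 between assessments; common improvement of 0.5 SD at T2 and 0.7 SD at T3; any true effect fully present at T2 and kept at T3; drop-out unrelated to outcome; children independent within therapy groups. The protocol gives none of these.

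**Formula.** Let p be an arm's drop-out by T3, s the share of it that occurs before T2, and m2 and m3 the mean changes from T1. The mean carried-forward change is (1 − p)·m3 + p(1 − s)·m2 + p·s·0.

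**True effect 0.50, equal 45% drop-out.** The expected estimate is 0.50 × (1 − 0.45s). Coverage is from simulation, with T3 analysed by baseline-adjusted ANCOVA.

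| Loss before T2 | Estimate | 95% interval coverage |
|---|---|---|
| none | 0.50 | about 95% |
| half | 0.39 | about 85% |
| all | 0.28 | about 47% to 49% |

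**No true effect.** With equal drop-out the expected difference is 0 and simulated type I error is near 5%. With unequal drop-out the spurious difference has size |p1 − p0| × [m3 − (1 − s)·m2]. For 40% v 55% or 50% v 35%, the gap is 0.15:

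- no loss before T2: 0.15 × (0.7 − 0.5) = 0.03 SD; type I error about 6%
- half: 0.15 × (0.7 − 0.25) = 0.07 SD; about 10% to 11%
- all: 0.15 × 0.7 = 0.105 SD; about 18% to 21%

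The sign reverses between the two drop-out patterns. With a smaller recovery (0.2 SD at T2, 0.3 SD at T3) at 40% v 55%, the largest spurious difference is 0.15 × 0.3 = 0.045 SD and type I error is about 5% to 7%.

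**Planned test.** The figures above come from T3 ANCOVA. With the group-by-time F test of a repeated-measures ANOVA at 40% v 55%, type I error was about 12% to 14% when the arm difference in loss arises before T2, 7% when the loss is split evenly, and 5.5% when the difference arises after T2.

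**Precision.** Counting 250 rather than 137.5 as observed alone gives sqrt(137.5 / 250) = 0.74, a 26% smaller standard error. In simulation it was about 22% to 34% smaller than in an observed-case ANCOVA.

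**The case against.** The strongest reply is that the damage is conditional. The document gives one drop-out figure and none by arm, and the control program was designed partly to avoid heavier loss in the control arm. With equal random loss and no true effect, carrying forward keeps type I error near 5%, and with a true effect it dilutes rather than inflates. The rule also applies only after mailed questionnaires and repeated reminders. All of this stands, and it is why no single type I error figure can be claimed. It does not justify the rule: dilution and false precision need no arm difference, and 45% remains the planning figure.

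A second reply is that the observed-case analysis was unbiased in these simulations and is close to the planned completer analysis, so the calculations do not show that a mixed model does better. That is correct. The simulated drop-out was unrelated to outcome, which is the setting that favours completers. The completer analysis is unbiased only if drop-out is unrelated to outcome given the variables in the model, and nothing in the document secures that.

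Two stronger readings should be resisted. A reader might infer that families enroll shortly after the violence ends, so that recovery is certain. The inclusion criteria require only that it has stopped by program start. A reader might also infer that the T2 payment, given "25,- after participating in the program and completing the second assessment", discourages program drop-outs from returning T2 data. The wording does not require finishing the program and may only describe timing.

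**Conclusion.** The point holds as a criticism of a rule that the document fixes. It is not a complaint about detail left to an analysis plan. At the expected loss, about 112 of 250 T3 values could be earlier scores treated as observed. Confidence is high on the method and limited on the numbers, which rest on the assumed correlation, recovery, timing and arm-specific loss.

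Under those assumptions the harm ranges from almost none in bias (all loss after T2, effect already stable) to loss of nearly half the true effect, with intervals that miss it about half the time. A reader might infer that carrying forward is always conservative, or that it always produces false positives. Neither follows: the direction depends on which arm loses more children and on how scores move. The completer analysis does not settle the matter if the two results disagree.

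**What to change.** Remove last value carried forward. Make the primary intention-to-treat analysis a linear mixed model on all available T1 to T3 scores of all randomised children, with an effect for therapy group. Alternatively, use multiple imputation based on T1 and T2 scores and on parent and teacher reports. Keep the completer analysis as supportive. Add a delta-shift sensitivity analysis, in which the missing T3 scores are made progressively worse or better, separately by arm, to see when the conclusion changes. Report drop-out by arm and by interval (T1 to T2, T2 to T3).

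The cost is a little more analysis work and confidence intervals that are honestly wider. No design change is needed. Data collection was still in progress (Status of the trial), and Ethical considerations provides for changes to be submitted as amendments.

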### Data analyses

Most analyses will be done using the software program SPSS. Intention-to-treat and completer analyses will be performed. Descriptive analyses will be carried out by standard methods. The change in behavior will be assessed on a continuous scale, taking into consideration the scale of the different variables. For analyses of the primary outcome measures, we plan to use ANOVA repeated measure analyses and the scores of the children in the intervention group will be compared with their own scores on a previous assessment, as well as with scores of children in the control group at the same assessment. Mediator and moderator models will be tested, using data of all children (intervention and control group). Analyses and reporting of the results will be done according to the CONSORT 2010 Statement-guidelines [60].

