### Trial objective

In order to justify broad implementation of a protocol led psycho-educational secondary preventive intervention program for children exposed to interparental violence in the Netherlands, empirical evidence is needed to show that children benefit from participation in this program. The present study will add to this evidence with a randomized controlled trial (RCT). Effectiveness is measured in terms of less posttraumatic stress symptoms, less internalizing and less externalizing behavioral problems. Because of the design of this study in which children in a trauma-focused intervention program are compared to children in a control program with only nonspecific factors, this study will provide insight in the need for trauma-focus in intervention. This knowledge can be used to improve care for children exposed to interparental violence. Potential mediating and moderating variables are investigated in order to evaluate underlying mechanisms of change and to identify predictors of effectiveness.

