#### Primary outcome measures

The main research question of this study is whether children who experienced interparental violence benefit from participating in the intervention program in terms of less posttraumatic stress symptoms, less internalizing behavioral problems and less externalizing behavioral problems in comparison with children participating in the control program.

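### The primary analysis sets a pre-post comparison within the intervention arm beside the randomised comparison and does not say which decides effectiveness

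*Protocol article*

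**What the plan says.** The protocol article's Primary outcome measures section states the main question as less posttraumatic stress and fewer internalizing and externalizing problems "in comparison with children participating in the control program". That is a between-arm question.

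The Data analyses section says of the primary outcomes that "we plan to use ANOVA repeated measure analyses". It then lists two comparisons in one sentence. One lies within the intervention arm: "the scores of the children in the intervention group will be compared with their own scores on a previous assessment". The other is between the arms and is joined to it without any ranking: "as well as with scores of children in the control group at the same assessment". It does not say which of them carries the conclusion. It names no group-by-time term and no T1 covariate.

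The Trial objective section says that, to justify broad implementation, "empirical evidence is needed to show that children benefit from participation in this program". According to the Demographic variables section, all instruments are given at T1, T2 and T3 apart from listed exceptions, and no primary outcome measure is among those exceptions.

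**The concern.** A fall in scores within the intervention arm is not a randomised comparison. It combines any program effect with whatever would have happened anyway. The protocol gives reasons to expect some improvement without the program: the Background says that distress after a frightening event is usually transient, and the inclusion criteria require that the violence has stopped before the program starts. The control arm exists to remove this ambiguity, and a test that leaves it out brings the ambiguity back. The Background also describes the earlier evidence on this program as quasi-experimental and gives the lack of a randomised trial as the reason for this one.

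Because the two comparisons are unranked, a null randomised contrast could be reported beside a significant pre-post fall, and the fall could be read as the benefit that the Trial objective section is looking for. The Control variables section adds measures of life events and treatment integrity to support attribution to the program. Neither deals with natural recovery.

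A second, smaller matter is that the between-arm contrast is not pinned down. A comparison at one assessment that ignores T1, a group-by-time test and a T1-adjusted comparison have different power.

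**Working it through.** **Inputs from the protocol**
- Effect size: "a conservative estimate of f = 0,25 [59] is made about the effect size". For two equal groups d = 2f = 0.5.
- Sample size: "Based on an alpha of .05, a power of .80 in a two tailed test, 48 subjects in each condition are needed".
- Allocation: "2/3 of all parent-child dyads will be randomized into the experimental arm and 1/3 into the control arm".
- Recruitment of 250 with about 45% drop-out from T1 to T3 (Sample size calculation): 250 × 0.55 = 137.5, about 138. Split 2:1, this is 92 v 46.

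**Assumed, because the protocol does not give them**
- Correlation r between T1 and follow-up: 0.3 to 0.7 for power, 0.5 to 0.7 for the pre-post test.
- Natural fall without a program effect: 0.2 to 0.5 SD.

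**The plan's own figure.** A plain two-group test needs n = 2 × (1.96 + 0.8416)² × 1 / 0.5² = 62.8, so 63 per arm (64 with the t distribution), not 48. With T1 as covariate at r = 0.5 the variance factor is 1 − 0.5² = 0.75, and 62.8 × 0.75 = 47.1, so 48. The between-group test of a repeated-measures ANOVA with three assessments and r = 0.6 also gives 48. The stated number therefore fits a method that uses the repeated scores, but only with a correlation the protocol does not state.

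**Pre-post test with no program effect.** The noncentrality is g × √n / √(2(1 − r)), where g is the natural fall in SD. It is referred to a t distribution with n − 1 degrees of freedom, two-sided 0.05. For g = 0.3, n = 48, r = 0.5: 0.3 × 6.93 / 1 = 2.08, probability 0.53.

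| Natural fall | n = 48, r = 0.5 to 0.7 | n = 92, r = 0.5 to 0.7 |
|---|---|---|
| 0.2 SD | 0.27 to 0.42 | 0.48 to 0.69 |
| 0.3 SD | 0.53 to 0.75 | 0.81 to 0.96 |
| 0.5 SD | 0.92 to 0.99 | above 0.99 |

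**Between-arm power at one follow-up, d = 0.5, 92 v 46, before clustering.** The noncentrality is 0.5 / √(v × (1/92 + 1/46)) = 2.77 / √v, with 136 degrees of freedom. The variance factor v is 1 when T1 is ignored, 2(1 − r) for a change score (equal to group-by-time with two assessments), and 1 − r² for ANCOVA on T1.

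| Contrast | r = 0.3 | r = 0.5 | r = 0.7 |
|---|---|---|---|
| T1 ignored | 0.785 | 0.785 | 0.785 |
| Change score / group-by-time | 0.642 | 0.785 | 0.944 |
| ANCOVA on T1 | 0.822 | 0.888 | 0.971 |

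The gain of ANCOVA over group-by-time is 0.180 / 0.103 / 0.027. Over a comparison that ignores T1 it is 0.037 / 0.103 / 0.186.

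**The case against.** The strongest reply is that the two listed comparisons are an informal description of the within and between factors of a repeated-measures ANOVA. The same sentence plans the randomised comparison, the Primary outcome measures section defines the main question against the control program, and the sample size rests on differences between programs. A condensed article may also leave the exact contrast to a fuller document. Much of this stands. The control comparison is the declared question, and no section says that a within-arm fall alone would count as effectiveness. It does not remove the point, because the article itself writes a comparison confined to the intervention arm into the primary-outcome analysis and gives it equal standing.

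A reader might infer more than the protocol supports:
- That the arms are compared without baseline adjustment. This is not stated. A repeated-measures ANOVA can take T1 as a level of time, and the phrase about the same assessment says which scores are set side by side, not that T1 is left out of the model.
- That the trial is already short of power. Applying the 45% loss to 140 children would leave 77, but 250 less 45% is about 138, so 140 looks like the number after drop-out and the loss would probably be counted twice. At 92 v 46 even the comparison that ignores T1 has power 0.785, before clustering.
- That natural improvement must be large. Entry requires no symptom threshold, and the Background says that problems may develop even after the conflict has ended. Both weaken the case for a large fall, which is why the size is an assumption shown over a range.

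**Conclusion.** The point holds in a limited form. The primary-outcome analysis includes an unranked pre-post comparison within one arm that cannot separate program effect from natural recovery and does not answer the between-arm question. No T1-adjusted or group-by-time contrast is named as the deciding one. With an assumed natural fall of 0.3 SD and correlation 0.5 to 0.7, a significant within-arm result is more likely than not even if the program does nothing.

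On power, ANCOVA on T1 does better than both alternatives at each correlation checked. How much better depends on a correlation the protocol does not give. If the planned ANOVA means group-by-time, the gain is 18 points at 0.3 and under 3 points at 0.7. All figures take d = 0.5, a single follow-up and no clustering.

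This should be changed, but it does not undermine the design: the randomised comparison is planned and the data for it are collected.

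**What to change.** In the Data analyses section, name the primary estimate as the intervention-minus-control difference at T2 and at T3, from one model with the T1 score of the same measure as covariate. State that this contrast decides effectiveness. Report change within each arm descriptively, and say that it is not evidence of effectiveness.

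The cost is wording only, since the primary instruments are already given at T1. How to allow for therapy groups in the model is a separate clustering question and is not settled by this change.

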### Protection of data privacy

All parent-child dyads participating in the study will be assigned a number. Key lists will be stored separately from the data and will be deleted after final data analyses. Data will be analyzed in a way that no conclusions can be drawn about individual participants. All data are stored in lockable cabinets in lockable rooms. All employees and students working within the project sign a statement in which they declare not to disclose any information about research participants to a third party. Only if the safety of a parent or child is in danger, these concerns will be shared with the participating organization where the program is carried out.

### Publication policy

We plan to publish the results of this study in peer-reviewed, international journals. To make the results also available for Dutch policy makers and service providers, we plan to publish the results in (Dutch) journals within the field of youth mental health care. Results will be presented at international scientific conferences, as well as at national conferences within the field of youth care and mental health care.

